**Methods:**

This stepped wedge randomized controlled pilot study will be conducted over 2 years in collaboration with primary care clinics. Eligible participants are patients with type 2 diabetes who are receiving health care from participating clinics. Clinics will be randomly assigned to an implementation date and will begin with patients enrolling in the control period while receiving standard care, then cross over to the intervention period where patients receive standard care plus the SMart-D intervention for over 12 weeks. Focus groups or interviews will be conducted with clinicians and patients after study completion. Qualitative data will be analyzed using NVivo. Outcomes on self-care behavior changes will be measured with the Summary of Diabetes Self-Care Activities scale and clinical changes will be measured using laboratory tests. A generalized linear mixed-effect model will be used to compute time effect, clustering effect, and the interaction of the control and intervention periods using SAS (version 9.4; SAS Institute).

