#### Patient Recruitment and Consent Process

This study will recruit 80 patients from 10 clinics, approximately 8 patients from each clinic. We expect to have approximately 5 to 6 patients complete this study from each clinic giving a 70% (n=56) study completion rate. The power calculation was conducted by using the linear mixed effect modeling of the R (R Foundation for Statistical Computing) package “*swdpwr*,” which gives power of 0.95 for the alternative hypothesis treatment effect change of 0.005 (2-sided type I error 0.05). The recruitment strategy includes a letter and flyer to be sent by the clinics with the research team’s contact information. Study information will be provided to those who reach out to a research team member with their interest and an opt-out contact will be applied after 3 days of receiving the letter. A member of the research team will arrange a time to meet with eligible patients to discuss the option to participate in this study, complete the informed consent procedure, complete this study’s screener, and enroll them in this study if the individual is both eligible and interested. All patients will have the option of completing the consent and confidentiality forms in English or Vietnamese language. Upon full study enrollment, a member of the research team will collect baseline data.

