The secondary outcomes are self-reported changes in behaviors and clinical test results, which will be compared to determine intervention maintenance and effectiveness. Repeated outcome measures will be assessed at 5 points in time. The translated and validated SDSCA revised scale [32] will be used to measure behavioral changes and assess 5 topics: diet, physical activity and exercise, blood glucose testing, foot care, and smoking. The average interitem correlations within scales were high (mean *r*=0.47) with the exception of specific diet; test-retest correlations were moderate (mean *r*=0.40). Correlations with other measures of diet and exercise generally supported the validity of the SDSCA subscales (mean *r*=0.23). Triglyceride, low-density lipoprotein, high-density lipoprotein, hemoglobin A_1c_, BMI, weight, and blood pressure will be used to measure clinical changes, which will be obtained from the participants’ medical records. Participants will be monitored for an additional 9 months via chart reviews and self-report using the SDSCA scale to determine whether any improvements observed at completion of the intervention will still be evident.

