#### Data Analysis

To evaluate the first hypothesis, descriptive statistics will be used to analyze the acceptability and feasibility of the intervention, which include the proportion of individuals who met the criteria, proportion of eligible participants who agreed to participate, the proportion of mHealth responses completed, and attrition rate at follow-up periods. A linear regression model will be used to examine the association of response rate and attrition rate with other predictors. To evaluate the second hypothesis, continuous variables will be calculated using descriptive statistics including quantiles, mean, and SD. To examine the association of continuous outcome variables and other predictors, a linear mixed effect model will be used to examine time effects, clustering effects, and the interaction of the two. Transformation of outcome variables will be conducted to normalize the nonnormal distributions. To examine the association of categorical outcome variables and other predictors, a generalized linear mixed effect model will be used to examine time effects, clustering effects, and the interaction of the two. In order to handle missing values, sequential multiple imputation will be performed before the analysis. SAS (version 9.4; SAS Institute) will be used for statistical analysis.

To analyze qualitative data from the focus groups and interviews, field notes will be transcribed for coding and analysis. Focus groups and interviews conducted in Vietnamese will be translated into English by the research assistant and verified by the PI before coding and analyzing thematically. Prior to analyzing the transcripts, the researchers will read the transcripts at least twice and compare them with the field notes to ensure accuracy and completeness. Selected transcripts will be reviewed by an experienced qualitative researcher to compare the consistency in developing a coding schema. The NVivo (Lumivero) software will be used to manage and analyze qualitative data.

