## Discussion

This study is driven by two hypotheses: (1) at least 50% (n=5) of eligible clinics and 50% (n=40) of eligible patients who are invited will participate, and at least 70% (n=56) of patients will complete the program, and (2) patients who receive the intervention will have improved self-care behaviors and improved clinical test results with at least 75% (n=60) of the patients maintaining improved outcomes at follow-up visits compared with baseline, and participants will verbalize that the intervention is feasible and acceptable. This protocol was designed with an interprofessional research group that has many strengths. An overall strength is the stepped wedge design, which allows participating clinics to be randomized with an opportunity for all consented patients to participate in the intervention. The staggering of clinic implementation allows the research team to train clinic staff and monitor potential implementation issues. The mixed method and longitudinal design provide insights into long-term outcomes over time.

Another strength of this protocol is this is the first Vietnamese DSMES intervention to be implemented in collaboration with primary care clinics that leverages mHealth technology to address the barriers of language and cultural differences. Vietnamese-speaking individuals have few opportunities to participate in health-related randomized clinical trials. This protocol allows that opportunity because it is offered in the Vietnamese language to promote self-determination and independence, and improve self-management strategies.

Further, 1 limitation of the stepped wedge design is that patients of clinics that were randomized for implementation later will have to wait months before receiving the intervention. This waiting period may reduce engagement with the researchers and may increase attrition rates. Another limitation is the repeated measurements of questionnaires and clinical tests may lead to a higher respondent burden on patients and clinic staff.

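### Unrestricted multiple imputation, combined with a maintenance target of 60 out of all 80 enrolled when 56 are expected to complete, leaves patients without follow-up data, or who never started the program, open to being counted as maintainers

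*Protocol article*

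**What the plan says.** All references are to the protocol article.

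- **Missing data (Data Analysis).** After the descriptive and model-based methods for both hypotheses, the section states: "In order to handle missing values, sequential multiple imputation will be performed before the analysis". It limits this neither by reason for missingness nor by outcome or hypothesis.
- **Target (Discussion; the same figures stand in the abstract's Results).** Hypothesis 2 reads in part: "patients who receive the intervention will have improved self-care behaviors and improved clinical test results with at least 75% (n=60) of the patients maintaining improved". The criterion is "at least 75% (n=60) of the patients maintaining improved outcomes at follow-up visits compared with baseline".
- **Sample (Patient Recruitment and Consent Process).** "This study will recruit 80 patients from 10 clinics, approximately 8 patients from each clinic", and "We expect to have approximately 5 to 6 patients complete this study from each clinic giving a 70% (n=56) study completion rate".
- **Enrollment before crossover (abstract, Methods).** Clinics "begin with patients enrolling in the control period while receiving standard care, then cross over to the intervention period". A patient can therefore leave before receiving any of the program.
- **Attrition (Discussion).** On patients of later clinics: "This waiting period may reduce engagement with the researchers and may increase attrition rates".
- **Follow-up (Outcome Measures).** "Participants will be monitored for an additional 9 months via chart reviews and self-report using the SDSCA scale". Laboratory values, weight, BMI and blood pressure come from medical records. The Maintenance rows of Table 1 name clinical assessments and laboratory results as the method for sustained patient outcomes.

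Outcome Measures lists maintenance among the primary RE-AIM outcomes. The behavioral and clinical measures from which it is judged are called secondary.

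**The concern.** The maintenance criterion asks how many patients who received the program still show improvement later. Three features of the plan pull against that question.

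First, the bracketed count takes everyone enrolled as denominator, not those who received the program. Second, that count exceeds the expected number of completers. Third, the only stated way of dealing with absent values is to impute them all before analysis. Sequential imputation in its usual form assumes data are missing at random. A patient with no follow-up values is then given values typical of patients with similar observed data who stayed. If people leave because they have disengaged from self-management, their true outcomes are likely to be worse than that.

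Patients lost during the wait are the clearest case. Imputing post-program values for someone who never had the program does not answer hypothesis 2, whatever the imputation model.

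At stake is whether the maintenance share of a pilot intended to inform scale-up reflects loss of patients or is largely insulated from it.

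**Working it through.** **1. The plan's own counts.** Enrolled: 80. Completers: 0.70 × 80 = 56, as stated. Non-completers: 80 − 56 = 24. Target: 0.75 × 80 = 60, as stated. So the 75% is taken over all 80.

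**2. Target against completers.** If every completer maintained, the share would be 56/80 = 70%, below 75%. Reaching 60 needs at least 60 − 56 = 4 of the 24 non-completers (4/24 = 17%), whether from chart data or from imputed values.

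**3. What default imputation adds.** Suppose completers maintain at 75% (42 of 56) and all 24 non-completers lack follow-up data. Both are assumptions. Imputing at about the completers' rate adds 24 × 0.75 = 18, giving (42 + 18)/80 = 60/80 = 75%, exactly the target.

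**4. If lost patients do worse.** With q the true maintenance rate among the 24 (assumed), the true share is (42 + 24q)/80 and the overstatement is 0.30 × (0.75 − q).

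| q (assumed) | True share | Imputed share | Overstatement |
|---|---|---|---|
| 50% | 54/80 = 67.5% | 75% | 7.5 points |
| 37.5% | 51/80 = 63.8% | 75% | 11.2 points |
| 0% | 42/80 = 52.5% | 75% | 22.5 points |

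**5. If only some non-completers lack data.** When m of the 24 have no follow-up values, the overstatement is about (m/80) × (0.75 − q). With m = 12 (assumed) and q = 50% it is 0.15 × 0.25 = 3.75 points; with q = 0% it is 0.15 × 0.75 = 11.25 points. The documents do not give m.

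**6. Simulation check.** The settings were: 80 patients, a 30% chance of dropping out with only the baseline value observed, 20 sequential-regression imputations and 500 runs. The outcome had baseline mean 8 and SD 1.2; those who stayed improved by 0.7 on average and those who left by nothing. Maintained meant a last value below baseline. All these values are assumptions. True maintenance was 78% in those who stayed and 50% in those who left. Imputation gave those who left 76%, and 77% overall against a true 69%, about 8 points too high. The 50% among patients with no average change arises from random variation alone.

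**7. Denominator.** With S starters and outcome data on 56, the highest share when patients without data count as not maintained is 56/S. This reaches 75% only if S ≤ 56/0.75 = 74.7, that is, at most 74. With S = 80 it is 70%.

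**The case against.** The case on the other side is substantial.

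- **Leaving is not the same as missing.** Laboratory values, weight and blood pressure come from charts, with nine further months of chart review. A patient who stops answering messages may still have observed values. This stands, and it confines the problem mainly to the self-reported self-care scale and to patients with no further chart data.
- **The link to the 75% is inferred.** The imputation sentence follows the mixed-model text and does not mention the maintenance proportion. This stands. The sentence nevertheless has no restriction, and maintenance is judged from the outcomes to which it applies.
- **The imputation details may be in an analysis plan that is not shown.** The missing-at-random assumption and the imputation model are ordinary content of such a plan, and their absence here is no fault. What can be judged from the article is the rule as worded, beside a target count that does not fit the plan's own completers or the group named in its hypothesis.
- **Imputation uses each patient's observed values.** True: a patient with a poor 3-month result would not simply receive the completers' rate. The protection is weak for someone with baseline data only.
- **Attrition is reported openly.** Hypothesis 1 has its own completion target, attrition rates are to be tabulated, and the article does not make the 75% a formal go/no-go rule. This limits the consequences but does not correct the maintenance share.

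A reader might infer something stronger: that all 24 non-completers would be given completers' outcomes, that a known part of them leave before starting, and that the share is therefore overstated by 11 to 22.5 points. The documents do not support this. They give no count of patients without data, say only that waiting may increase attrition, and give no maintenance rate for lost patients.

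**Conclusion.** The point holds in limited form. As worded, the imputation rule has no exception. The maintenance count of 60 is set against all 80 enrolled, exceeds the 56 expected completers, and does not match a hypothesis about patients who receive the program. Under default missing-at-random imputation, patients with no follow-up data, including any lost before their clinic crossed over, would be credited at about the rate of similar patients who stayed.

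The mismatch between 60 and 56 is certain, being arithmetic on stated figures. The size of any overstatement is not known. The range of 7.5 to 22.5 points in the working rests on three assumptions: all 24 non-completers lack data, completers maintain at 75%, and lost patients maintain at between 50% and 0%. Available chart data would reduce it, and it vanishes if lost patients maintain as well as similar patients who stayed. The direction is toward too favourable a result if loss reflects disengagement, which the article raises as a possibility but does not quantify.

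**What to change.** In Data Analysis, add a short rule for the maintenance criterion:

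1. Take as denominator the patients who started the program. Do not impute program outcomes for patients lost before starting; report their number separately.
2. Use chart values wherever they exist, whether or not the patient stayed engaged with the program.
3. Report three results side by side: the imputed share, the observed count with its own denominator, and a count in which starters without follow-up data are treated as not maintained. Describe the 75% target as robustly met only if it holds across all three.
4. Restate n=60 so that it agrees with the chosen denominator and the 56 expected completers. For example, 75% of 56 is 42.

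The cost is a few sentences and one extra tabulation, with no new data. The stated share may become less favourable. Counting patients without data as not maintained is itself a strong assumption: if all 80 start and 24 have no data, it cannot exceed 70%, so the target would be out of reach by construction. It should therefore serve as a lower bound beside the imputed share, not as the sole decision rule.

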### Intervention Fidelity

The intervention uses 3 fidelity checks to ensure that participants have received the intended information. First, the mHealth SMS text messages will be distributed automatically. Second, progress will be monitored and followed up with participants who abruptly stop reading or responding to our SMS text messages. Third, the nurse coaching call sessions will be monitored randomly by the PI, who will make note of any deviations and will provide further training for the nurse. These fidelity assessments are structured to ensure the intervention is implemented as intended during the delivery process.

### Ethics Approval

Ethical approval has been granted by the University of Oklahoma Health Sciences Center institutional review board on October 25, 2022 (IRB#14700). Permission from the large health systems and each clinic has also been granted. The SMart-D intervention involves research with an ethnic minority and understudied population. To ensure the needs of this population are met, the research team has led a prior project with members of this community who contributed to the design, development, and implementation of this study. Ethical procedures include steps for continuation of health education for participants after study completion by coordinating with local health departments to refer participants to the existing and structured Total Wellness program of Oklahoma. Baseline data and lessons learned will be presented at conferences, and study outcomes will be published in scientific journals. Study results will also be communicated to relevant health care professionals and to the US Vietnamese community through lectures, posters, and pamphlets.

## Results

Planning for the SMart-D study began in January 2022, clinic recruitment began October 28, 2022, and patient recruitment began November 4, 2022. Data collection of outcome measures will be completed in 2024. This study was funded during July 2022 to June 2024. As of August 24, 2023, 10 clinics and 60 patients were enrolled in this study. The results are expected to be available by 2025 and will demonstrate intervention acceptability, feasibility, effectiveness, and sustainability.

## Discussion

This study is driven by two hypotheses: (1) at least 50% (n=5) of eligible clinics and 50% (n=40) of eligible patients who are invited will participate, and at least 70% (n=56) of patients will complete the program, and (2) patients who receive the intervention will have improved self-care behaviors and improved clinical test results with at least 75% (n=60) of the patients maintaining improved outcomes at follow-up visits compared with baseline, and participants will verbalize that the intervention is feasible and acceptable. This protocol was designed with an interprofessional research group that has many strengths. An overall strength is the stepped wedge design, which allows participating clinics to be randomized with an opportunity for all consented patients to participate in the intervention. The staggering of clinic implementation allows the research team to train clinic staff and monitor potential implementation issues. The mixed method and longitudinal design provide insights into long-term outcomes over time.

Another strength of this protocol is this is the first Vietnamese DSMES intervention to be implemented in collaboration with primary care clinics that leverages mHealth technology to address the barriers of language and cultural differences. Vietnamese-speaking individuals have few opportunities to participate in health-related randomized clinical trials. This protocol allows that opportunity because it is offered in the Vietnamese language to promote self-determination and independence, and improve self-management strategies.

Further, 1 limitation of the stepped wedge design is that patients of clinics that were randomized for implementation later will have to wait months before receiving the intervention. This waiting period may reduce engagement with the researchers and may increase attrition rates. Another limitation is the repeated measurements of questionnaires and clinical tests may lead to a higher respondent burden on patients and clinic staff.

In conclusion, this study will improve understanding of the implementation process, demonstrate the potential effectiveness of the intervention, accelerate the pace of moving evidence-based interventions to practice among the Vietnamese population, and potentially provide a replicable implementation model that can be culturally tailored to other non-English speaking ethnic minorities. Furthermore, successful study results may be implemented across other localities and states and across both primary care and specialty clinics.

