**Results:**

We hypothesize that (1) at least 50% (n=5) of eligible clinics and 50% (n=40) of eligible patients who are invited will participate, and at least 70% (n=56) of patients will complete the program, and (2) patients who receive the intervention will have improved self-care behaviors and clinical test results with at least 75% (n=60) of the patients maintaining improved outcomes at follow-up visits compared with baseline, and participants will verbalize that the intervention is feasible and acceptable. As of August 2023, we enrolled 10 clinics and 60 patients. Baseline data results will be available by the end of 2023 and outcome data will be published in 2025.

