#### Randomization

Because individual randomization is not feasible due to potential contamination of the intervention for control participants, this study will use a programmatic roll-out in a stepwise fashion where each clinic that is not yet receiving the intervention will function as a control. Another reason for the selection of a stepped wedge design is that the measurement of outcomes is at the clinic level and individual patient level. Randomization of the intervention sequence will be conducted at the level of the clinics with computer-generated assignment using SAS (version 9.4; SAS Institute) by a statistician blinded to the identity of the clinics and not involved in the intervention delivery. The clinics will be randomized from 1 through 10 and will be allocated a date of implementation which will be concealed until interventions are assigned. Clinics will be informed that the order of allocation to the intervention will be unknown in advance of randomization.

During the initial control period, no clinic will be exposed to the intervention. Subsequently, at each 3-month interval, 1 clinic will transition from the control to the intervention period. This staggered schedule will allow for optimal training, implementation, and supervision of clinic staff. The process will continue until all 10 clinics have crossed over to receive the intervention. Figure 1 illustrates this study’s procedures.

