**Adoption: intervention adoption at clinic and patient level**							
	Percentage of eligible clinic sites who participated	Enrollment data	✓	N/A	N/A	N/A	N/A
	Barriers and facilitators to adoption	Focus groups or interviews	✓	N/A	N/A	N/A	N/A

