#### Outcome Measures

The primary outcomes are the degree of reach, effectiveness, adoption, implementation, and maintenance measured by using the RE-AIM framework [31]. Reach is the ability to recruit patients and will be determined by assessing the number of people who received an invitation over the number of those who may be eligible to participate in the same clinic. Data sources include the number of invitations and the number of eligible patients seeking care at the clinic. Adoption will be measured by the proportion of clinicians who used the program and the number of patients who participate in the intervention by assessing the number of enrolled participants over the number of those invited, 3 months after the initiation of the intervention. Program implementation will be assessed by conducting a focus group or interview with the clinicians and patients separately at each clinic to gather feedback. Differences and similarities will be compared within and across clinics to identify emerging themes. Barriers and facilitators to program adoption by clinics will also be identified. See Table 2 for postintervention focus group or interview questions.

**Table 2 table2:** Postintervention focus group or interview questions for participants.

Measures	Interview questions
Acceptability	How would you describe your experience of taking part in this tailored DSMES^a^ program? What aspect of the program did you like the most? What was your favorite session? Suppose a friend of yours was diagnosed with diabetes and came to you for advice. What would you tell them about this DSMES program?
Process of change	What did you learn from this program? How has your perspective of living with diabetes changed since completing the program? What differences have you noticed in your life as a result of taking part in this DSMES program?
Barriers	What kind of difficulties did you experience taking part in this DSMES program?
Improvement	What did you least like about the program? What do you think could be improved about this DSMES program?
Implementing change	How often do you practice the self-care behaviors such as following a healthy eating plan, testing your blood sugar, caring for your foot, etc. learned from this program?

^a^DSMES: diabetes self-management education and support.

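### The counts n=40 patients and n=5 clinics in hypothesis 1 are half of the recruitment targets, not half of those invited or eligible, and do not fit with n=56 completers

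*Protocol article*

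**What the plan says.** The first hypothesis appears in the Results paragraph of the Abstract and again in the Discussion. It sets three thresholds, each a percentage followed by a count. The two for participation read "at least 50% (n=5) of eligible clinics and 50% (n=40) of eligible patients who are invited will participate". The third, in the same sentence, is that "at least 70% (n=56) of patients will complete the program".

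The recruitment plan, under Patient Recruitment and Consent Process, is "This study will recruit 80 patients from 10 clinics, approximately 8 patients from each clinic". It continues: "We expect to have approximately 5 to 6 patients complete this study from each clinic giving a 70% (n=56) study completion rate". The Randomization section uses all ten clinics: "The clinics will be randomized from 1 through 10 and will be allocated a date of implementation".

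The measures are defined elsewhere as proportions. Outcome Measures describes patient participation as "assessing the number of enrolled participants over the number of those invited", and the Adoption rows of Table 1 list "Percentage of eligible clinic sites who participated". Data Analysis evaluates the first hypothesis descriptively, including the share of eligible people who agree to take part. The article's Results section reports that by 24 August 2023 "10 clinics and 60 patients were enrolled in this study".

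**The concern.** Half of the invited patients is 40 only if 80 are invited, and half of the eligible clinics is 5 only if 10 are eligible. The article gives 80 and 10 a different meaning: they are the patients to be recruited and the clinics to be randomized. The counts therefore seem to rest on the wrong denominators.

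These are the stated success thresholds for feasibility, and they concern RE-AIM measures that Outcome Measures names as primary. A threshold printed in two forms that can give opposite answers leaves the final report free to cite either one. The count is the easier form to meet, because it depends only on how many enrol and not on how many were approached.

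**Working it through.** **Inputs**

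- Participation thresholds: 50% (n=40 patients) and 50% (n=5 clinics), from the Abstract and Discussion.
- Completion threshold: 70% (n=56), from the same sentence and from Patient Recruitment and Consent Process.
- Recruitment target: 80 patients from 10 clinics, from Patient Recruitment and Consent Process; 10 clinics randomized, from Randomization.
- Enrolment by August 2023: 60 patients and 10 clinics, from Results.
- Numbers invited or eligible: not stated. They are treated below as assumptions, over a range.

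**Step 1. Reproduce the stated counts** (count = percentage × base)

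- Patients: 0.50 × 80 = 40.
- Clinics: 0.50 × 10 = 5.
- Completers: 0.70 × 80 = 56.

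All three match exactly, and each count fixes its base: 40/0.50 = 80, 5/0.50 = 10, 56/0.70 = 80.

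**Step 2. Compare the bases**

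For n=40, the 80 must be patients invited. For n=56, the 80 must be patients enrolled. Both can hold only if everyone invited enrols (80/80 = 100%), which leaves a 50% participation threshold with nothing to test.

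**Step 3. Chain the minima**

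If exactly 40 take part, 70% completion gives 0.70 × 40 = 28. The stated 56 would be 56/40 = 140% of participants.

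**Step 4. Compare the count with the rate, using reported enrolment**

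Rate = 60 / number invited (assumed).

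| Invited (assumed) | Rate with 60 enrolled | n=40 met? | 50% met? |
|---|---|---|---|
| 80 | 75% | yes | yes |
| 120 | 50% | yes | yes |
| 160 | 37.5% | yes | no |
| 300 | 20% | yes | no |

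The switch is at 60/0.50 = 120 invited. For clinics, 10 enrolled is 100% of 10 eligible, 50% of 20 and 25% of 40. The count of 5 is met in each case, and the 50% rate fails above 10/0.50 = 20 eligible clinics.

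**Step 5. Illustration at full enrolment**

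If 80 patients and 10 clinics enrol, the 50% criteria are met only with at most 80/0.50 = 160 eligible patients invited and at most 10/0.50 = 20 eligible clinics.

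**The case against.** The strongest reply is that the operative criterion is already a proportion. The hypothesis puts the percentage first, and Outcome Measures, Table 1 and Data Analysis all define participation as a rate. Outcome Measures also names the number of invitations as a data source. No section says that the count decides. On this view the counts are loose parentheses, and randomization, sample size and the effectiveness models do not depend on them. The article also sets no formal stop/go rule on these thresholds.

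Much of this stands, and it rules out several stronger readings that a reader might infer:

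- *That the feasibility criterion has already been passed.* This is true only of the counts. The article gives no number invited or eligible, so whether the 50% rates were met is unknown.
- *That 40 and 5 contradict enrolling 80 and 10.* They are lower bounds, and enrolling 80 and 10 satisfies them. The inconsistency is narrower: one figure of 80 serves as both the invited and the enrolled base, and 40 participants cannot yield 56 completers.
- *That 160 and 20 are the correct denominators.* They are ceilings that apply only if enrolment reaches 80 and 10. The documents do not give the true denominators.
- *That the article is at fault for not planning confidence intervals around these proportions.* That is a reporting preference, commonly left to an analysis plan.

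The reply does not rescue the counts. If the percentage governs, n=40 and n=5 are wrong as printed and should go. Nor can 80 and 10 be read as numbers approached: the article recruits 80 at about 8 per clinic, takes its completion figure from them, and randomizes ten clinics.

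**Conclusion.** The point holds in this limited form. The counts attached to the 50% participation thresholds are computed from the recruitment targets and not from the numbers invited or eligible, and they are incompatible with the completion count in the same sentence (a minimum of 56 completers against a minimum of 40 participants, where 28 would be consistent).

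The practical effect is that the count and the percentage can disagree. With the reported 60 patients and 10 clinics, the counts are exceeded at any uptake, whereas the rates fail if more than 120 patients were invited or more than 20 clinics were eligible. Which case applies cannot be settled from the article. The arithmetic rests only on stated figures; the invited and eligible numbers are assumptions shown as a range.

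This is more than a clerical slip, because the figures are decision thresholds on primary outcomes. It does not affect the design or the effectiveness analysis. It should be corrected.

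**What to change.** In the Abstract and the Discussion:

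1. Delete n=40 and n=5. Let the proportions govern, in line with Outcome Measures, Table 1 and Data Analysis: enrolled over invited eligible patients at least 50%, and participating over eligible clinics at least 50%.
2. Take the denominators from the logged numbers of invitations and of eligible patients and clinics, and report them beside each rate.
3. State that 70% completion is of enrolled patients, which is 56 if 80 enrol.

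Do not replace the deleted counts with 160 and 20. They hold only at full enrolment and would again tie a rate to a fixed number.

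The cost is a text correction in two places. Invitations and eligible patients are already named as data sources, and eligible clinics must be counted for the Table 1 measure in any case. The 50% criterion itself does not change; what goes is the option of meeting it by count alone.
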